**General principles of dose adjustment**	
Grade 1–2	No adjustment required
Bleeding from any site classified as grade ≥2; Creatinine levels exceeding twice the upper limit of normal or baseline value but not exceeding three times the upper limit of normal or baseline value.	Suspension of surufatinib; Recovery to ≤ grade 1 within 4 weeks requires a reduction in dose level by one dose level
Grade 3 or higher bleeding; gastrointestinal perforation; nephrotic syndrome or hypertensive crisis; arterial thrombosis.	Permanent cessation of surufatinib
Other Grade 3 or 4 AE	Suspension of surufatinib; Recovery to ≤ grade 1 within 4 weeks requires a reduction in dose level by one dose level

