### Dosage adjustments

5.4

Toxic reactions should be classified based on NCI‐CTC AE version 5.0. Dosage adjustments of surufatinib should be guided by toxicity grading criteria. General principles include:
For adverse reactions, appropriate treatment should be administered to alleviate patient symptoms and signs. This may involve administering anti‐hypertensive drugs for hypertension and hepatoprotective drugs for liver function abnormalities.Pre‐existing adverse events at baseline, if deemed necessary by the researcher, will be adjusted according to changes in toxicity grading.In cases of multiple simultaneous adverse reactions, the most conservative dose adjustment plan should be implemented.Following adverse reactions, surufatinib dosage should not be re‐increased, and dosage should not be reduced more than three times during each patient's treatment course.The maximum duration of medication suspension due to toxic reactions is 4 weeks. If the adverse reaction decreases to ≤1 level within this period, dosage adjustment to resume medication is recommended. Specific dosage adjustment principles are outlined in the drug instructions. The principles of dosage adjustment are presented in Table 1.If researchers determine that a toxic reaction is unlikely to escalate to a serious or life‐threatening event, such as a rash, patients may continue treatment at the original dose without reduction or interruption. In the case of non‐hemolytic anemia, if better relief can be attained through interventions like blood transfusion, erythropoietin, and iron therapy, dosage reduction or treatment interruption may be unnecessary.

**TABLE 1 cam47131-tbl-0001:** Dose adjustment of surufatinib.

Dose adjustment gradients	
Original dose of surufatinib	300 mg qd po, q4w
The first reduction	250 mg qd po, q4w
The second reduction	200 mg qd po, q4w
The third reduction	200 mg/250 mg d1‐d21 po, q4w

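### Table 1 gives a grade 3–4 bleed two incompatible instructions: restart one dose level lower after recovery, or never restart

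*Protocol article*

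**What the plan says.** Section 5.4 (Dosage adjustments) sets general rules for surufatinib and refers to Table 1. The lower part of the table, on general principles, pairs types of event with actions. Three of its rows can bear on bleeding:

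- Grade 1–2 events, unqualified: "No adjustment required".
- "Bleeding from any site classified as grade ≥2", listed together with a bounded band of raised creatinine: suspend surufatinib, and then "Recovery to ≤ grade 1 within 4 weeks requires a reduction in dose level by one dose level".
- The row after that lists "Grade 3 or higher bleeding; gastrointestinal perforation; nephrotic syndrome or hypertensive crisis; arterial thrombosis" and assigns to all of these the action "Permanent cessation of surufatinib".

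A last row covers grade 3 or 4 events other than those already named.

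Four statements in the text of section 5.4 are also relevant:

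- "In cases of multiple simultaneous adverse reactions, the most conservative dose adjustment plan should be implemented".
- "The maximum duration of medication suspension due to toxic reactions is 4 weeks". Resuming at an adjusted dose is recommended if the reaction falls to grade 1 or below in that time.
- "Specific dosage adjustment principles are outlined in the drug instructions".
- A reaction judged unlikely to become serious or life-threatening, with rash as the example, may be managed at the original dose.

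**The concern.** The suspend-and-reduce row sets a lower limit for bleeding but no upper one, so it takes in grades 3 and 4. The next row claims those same grades for permanent cessation. Taken literally, the table both permits and forbids a restart after a severe bleed that has resolved.

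What is at stake is patient safety, not inference. The article itself treats bleeding as a hazard. Its exclusion criteria bar recent severe haemorrhage, recent haemoptysis and active gastrointestinal bleeding, and in the experimental arm surufatinib continues through an arterial procedure. Whether a patient may go back on the drug after a severe bleed should not depend on which of two adjacent rows the investigator reads first.

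**Working it through.** No arithmetic figure in the plan bears on this point. The check is to take each grade of bleeding that Table 1 names, find every row whose trigger it meets, and compare the actions.

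| Bleeding grade | Generic grade 1–2 row | Bleeding, grade 2 or higher | Bleeding, grade 3 or higher |
|---|---|---|---|
| 1 | no adjustment | – | – |
| 2 | no adjustment (generic default) | suspend, then reduce | – |
| 3 | – | suspend, then reduce | permanent stop |
| 4 | – | suspend, then reduce | permanent stop |

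The last row of the table does not apply to bleeding, because it is limited to other grade 3 or 4 events.

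**Grades 3 and 4.** Both applicable rows name bleeding, so neither is a general default to which the other is an exception. Follow one patient on 300 mg with a grade 3 bleed:

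1. At onset, both rows take the patient off the drug. There is no difference.
2. If the bleed has not fallen to grade 1 or below within 4 weeks, the suspend row offers no route back, and the permanent-stop row forbids one. There is again no practical difference.
3. If it has fallen to grade 1 or below within 4 weeks, the suspend row leads to a restart one level lower, which is 250 mg by the upper part of Table 1. The permanent-stop row forbids any restart.

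The conflict is therefore confined to step 3.

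**Is there a rule of precedence?**

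- The most-conservative rule is conditioned on several reactions occurring together. One bleed that meets two rows is one reaction.
- The general advice to resume after recovery within 4 weeks agrees with the suspend row and makes no exception for severe bleeding.
- The reference to the drug instructions does not say that they override Table 1, and the next sentence of section 5.4 presents Table 1 as the principles of adjustment.

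**Signs of a slip.** The creatinine trigger in the same cell has an upper bound, while the bleeding trigger has none although the next row takes over at grade 3. The likely intent is grade 2 in place of grade 2 or higher.

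**After the change.** With grade 2 in the suspend row, grades 3 and 4 meet only the permanent-stop row, and the contradiction between the two bleeding rows is gone.

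**The case against.** The strongest reply is that the table resolves itself when read as a whole. Only one reading gives every entry some effect: suspend and reduce at grade 2, stop for good at grade 3 or higher. If the suspend row governed grade 3, the bleeding entry under permanent cessation would be empty. The most-conservative rule, though it does not literally apply, shows which way the authors lean. The rows are headed as general principles, the specifics are left to drug instructions that are not shown, and this is a condensed article. For harm to follow, an investigator would have to pass over an explicit instruction to stop.

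Much of this stands. It makes the intended rule fairly clear, and it means that one cannot say from the article that investigators lack a workable rule. It does not remove the contradiction: inferring intent is different from having a stated rule, and if the drug instructions settle the matter, the printed table should agree with them.

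A reader might go further and infer that grade 2 bleeding is in the same state, because it also meets the generic grade 1–2 row. The table does not support giving that equal weight. The grade 1–2 row is a default and the bleeding row names a specific event, so the specific row is naturally read as the exception; otherwise it would do nothing at grade 2. A qualifier in the first row would be tidier, but its absence is not an incompatible instruction.

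**Conclusion.** The point holds for grade 3–4 bleeding. Two adjacent rows of Table 1 overlap, and for a bleed that recovers to grade 1 or below within 4 weeks they give opposite answers on restarting, with no stated precedence. It is a minor correction to a safety instruction, worth making because it removes a literal permission to rechallenge after a severe bleed.

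Two stronger conclusions should be avoided:

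- Counting grades 2, 3 and 4 as three of four in conflict would measure overlapping rows, not impact, and would put the grade 2 overlap on a par with the real contradiction.
- Saying that patients will be wrongly restarted, or how many, goes beyond the document. It gives no bleeding rate, and the drug instructions are not shown.

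No endpoint, sample size or analysis is affected. The conclusion assumes that the printed table is what investigators work from and that the grade 2 or higher sign is as the authors wrote it; nothing in the text suggests otherwise.

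**What to change.** In the suspend row of Table 1, change the bleeding trigger from grade 2 or higher to grade 2. The clinical lead should first confirm against the drug instructions that permanent cessation is intended from grade 3 upwards.

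Two optional clarifications could go in with it:

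- Label the first row as other grade 1–2 events, matching the wording of the last row.
- State in section 5.4 that the clause on continuing the original dose does not apply to events named in Table 1. Without this, the change to the suspend row does not by itself guarantee a single action for a grade 2 bleed, since an investigator could still invoke that clause.

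The cost is a wording change in one table cell, up to two short additions, and a brief notice to investigators. Nothing in the sample size or the analysis needs to be revisited.

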### Sample size and statistical analyses

5.5

Referring to the results of two phase III clinical studies of surufatinib (SANET‐p and SANET‐ep), the sample size calculation was performed using the log rank method on PASS, and the hazard ratio (HR) was set as 0.6 with a β error of 0.2 and a two‐sided α level of 10%. Patients were randomly assigned to the experimental group and control group in a 1:1 ratio, with an estimated dropout rate of 5% for each group. The study will last for 3 years, and the enrollment of subjects will occur in the first 2 years. Therefore, it is estimated that at least 62 patients are needed in the experimental group and 61 patients in the control group. A total of 123 patients and 96 events are needed in both groups.

The primary objectives are to determine BIRC‐assessed PFS. The secondary objectives are to determine investigator‐assessed PFS, OS, ORR, and safety. PFS is defined as the time from the beginning of treatment until the first observed disease progression or cancer‐related death. OS will be evaluated from the start of treatment to the death of patients. In this trial, ORR is defined as CR + PR according to RECIST 1.1. The 95% confidence intervals (CI) of the ORR will be calculated. The Kaplan–Meier method and a two‐tailed log rank test are used to evaluate PFS and OS.

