Surufatinib, a novel oral tyrosine kinase inhibitor that selectively targets VEGFR 1, 2, and 3, FGFR1, and so on, is being developed for the treatment of NETs. In 2020, two phase III clinical trials (SANET‐p and SANET‐ep) suggested that the median progression‐free survival (PFS) of the surufatinib group was significantly longer than that of the placebo group (pancreatic NETs: 10.9 months vs. 3.7 months, *p* = 0.0011; extrapancreatic NETs: 9.2 months vs. 3.8 months, *p* < 0.0001).^6^, ^7^ 84% of the enrolled patients had liver metastasis, and 66% of the patients had previously received antitumor treatment in the study. The most common treatment‐related adverse events were hypertension, diarrhea, proteinuria, and liver dysfunction. Thus, surufatinib was recommended as standard systemic treatment for locally advanced and metastatic NETs in China.^8^ Based on that NETs hepatic metastases receive most of their blood supply from the hepatic artery, transarterial embolization (TAE) represents a beneficial treatment option for control of symptoms as well as tumor growth,^5^ which is recommended by the guidelines of China and abroad. However, there is no prospective trial to confirm the feasibility of surufatinib plus TAE.^9^, ^10^, ^11^ To investigate this possibility, we planned a prospective study on the efficacy and safety of surufatinib combined with TAE compared to surufatinib monotherapy in patients with liver metastatic NETs, trying to explore a better regimen for NETs with liver metastasis and clinical guidelines.

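### On the cited surufatinib medians, 123 patients in a 3-year study are expected to give about 79–90 PFS events, short of the 96 stated, and 73–78% power instead of 80%

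*Protocol article*

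**What the plan says.** The sample-size paragraph (section 5.5) bases the calculation on the two phase III surufatinib trials. It gives these inputs:

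- Effect and power: "the hazard ratio (HR) was set as 0.6 with a β error of 0.2", with a two-sided alpha of 10%.
- Allocation 1:1, "with an estimated dropout rate of 5% for each group". No time scale is attached to the 5%.
- Calendar: "The study will last for 3 years, and the enrollment of subjects will occur in the first 2 years".
- Result: 62 experimental and 61 control patients, summarised as "A total of 123 patients and 96 events are needed in both groups".

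Section 5.5 does not give the control median used. The only surufatinib medians in the article are in the Background: 10.9 months in the pancreatic trial and, for the other, "extrapancreatic NETs: 9.2 months vs. 3.8 months", where the first figure is the surufatinib arm. Surufatinib alone is the control treatment here. The article does not say whether the primary analysis falls at the 96th event or at the end of year 3.

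**The concern.** A time-to-event sample size has two steps. The first turns the hazard ratio, alpha and power into a number of events. The second turns events into patients, using the event rates, the accrual pattern, the follow-up and the losses. The first step can be checked from the text and is right. The second can be checked against the medians of the trials named as its source, and on those medians 123 patients are too few to give 96 events in the stated three years.

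The primary endpoint is at stake. If the trial closes on the calendar, it is analysed with fewer events and less power than stated. If it waits for 96 events, it runs past three years. Because the article does not say which applies, the choice could end up being made late, in an open-label trial, by people who have seen how the patients are doing.

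**Working it through.** **Inputs.** From section 5.5: HR 0.6, power 80%, two-sided alpha 0.10, 62 and 61 patients, accrual A = 24 months, study length T = 36 months, dropout 5%. From the Background: surufatinib medians 9.2 and 10.9 months. Assumed, because not stated: these medians apply to the control arm, accrual is uniform and PFS is exponential.

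**1. Event target (the plan's own figure).** Schoenfeld: d = 4(z₀.₉₅ + z₀.₈₀)² / (ln 0.6)² = 4(1.645 + 0.842)² / 0.5108² = 94.8, so 95. With 96 events, power = Φ(√96/2 × 0.5108 − 1.645) = 80.4%. The 96 is reproduced to within rounding and is not in dispute.

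**2. Expected events at month 36 without dropout.** With hazard λ = ln 2 / median, the chance that a patient has an event by month T is

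P = 1 − [e^(−λ(T−A)) − e^(−λT)] / (λA).

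- Control median 9.2: λ = 0.0753 (control) and 0.0452 (experimental). P = 0.813 and 0.645. Events = 61 × 0.813 + 62 × 0.645 = 49.6 + 40.0 = 89.6.
- Control median 10.9: λ = 0.0636 and 0.0382. P = 0.761 and 0.586. Events = 46.4 + 36.3 = 82.7.

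**3. Dropout and power.** The 5% can be read in three ways: spread over 36 months as a constant censoring hazard, as 5% per year, or as a flat loss of 5% who contribute no events (multiply by 0.95). Power = Φ(√d/2 × 0.5108 − 1.645).

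| Dropout reading | Events, median 9.2 | Power | Events, median 10.9 | Power |
|---|---|---|---|---|
| None | 89.6 | 78.0% | 82.7 | 75.1% |
| 5% over 36 months | 88.4 | 77.5% | 81.6 | 74.6% |
| 5% per year | 86.2 | 76.6% | 79.4 | 73.6% |
| Flat 5% loss | 85.1 | 76.2% | 78.6 | 73.2% |

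The shortfall against 96 is about 6 to 17 events. A log-rank simulation (4,000 trials per scenario; medians 9.2, 10 and 10.9; no dropout, flat loss and 5% per year) gave the same picture. Mean events were 79–90 and power was 73–78%. Trials with 96 events by month 36 made up at most 11% without dropout and under 3% with it.

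**4. What would make 96 events in 36 months come true.** Solving for the control median with 123 patients and uniform accrual gives 7.8 months (no dropout), 7.5 (5% over 36 months), 7.1 (5% per year) or 6.7 (flat loss). All lie below 9.2 and 10.9.

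**5. When 96 events would arrive.** With 123 patients, at about month 40 (median 9.2) to 45 (median 10.9) without dropout, and about month 44 to 49 with a flat 5% loss.

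**6. Sensitivity to accrual.** If accrual is front-loaded within the same 24 months, with density falling as exp(−2x), x being the fraction of the accrual period elapsed, expected events without dropout are 96.0 at median 9.2 and 89.4 at 10.9. A flat 5% loss takes the first to 0.95 × 96.0 = 91.2.

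**The case against.** The strongest reply is that the control median is inferred. Section 5.5 refers to the two trials without saying which value was entered. Those trials were not confined to liver metastases (the Background gives 84%), whereas this one requires them in every patient and admits performance status up to 2, so a shorter planning median is conceivable. An article may also leave the software inputs to the full protocol. This stands as a limit on certainty: the shortfall is conditional on the cited medians. It does not remove the point, because the article names those trials as the basis and gives no reason for a median of 6.7–7.8 months.

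It can also be said that the flat 5% loss is the harshest reading of dropout. That is true, and the low ends of the ranges come from it or, almost equally, from the annual reading. Yet with no dropout at all the expected count is still 83–90.

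Three stronger readings are tempting, and the document does not support them:

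- *That 96 events and a three-year study are incompatible.* This holds only under uniform accrual, exponential PFS and the cited medians. Clearly front-loaded accrual reaches 96 at median 9.2 without dropout.
- *That 123 patients each followed for three years would fall short.* That is not the design. Follow-up runs from 12 to 36 months. With a full 36 months each, about 101–107 events would be expected (96–101 with a flat 5% loss), which meets the target.
- *That the trial will be underpowered.* The text says 96 events are needed and does not order an analysis at month 36. If three years is only a projection, the power is kept and the calendar slips.

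**Conclusion.** The point holds in conditional form. The 96 events are right for the stated effect, alpha and power. On the only surufatinib medians in the article, with uniform accrual and exponential PFS, 123 patients in the stated calendar are expected to give about 83–90 events without dropout and about 79–88 with 5% dropout, for 73–78% power overall against the 80% stated. No reading of the dropout rate closes the gap.

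The size is moderate: about 2 to 7 percentage points of power, or about 4 to 13 months of extra follow-up. Type I error and the validity of the log-rank test are not affected. Confidence in the arithmetic is high. Confidence that the calculation itself used inconsistent inputs is only moderate, because the median entered is not stated. This should be fixed, but it does not by itself put the trial's conclusion in doubt.

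**What to change.** State in section 5.5 the control-arm median PFS, the accrual pattern and the time scale of the 5% dropout used in the calculation. If the median is below the cited 9.2 and 10.9 months, give the reason. Then choose one of two options before any outcome data are reviewed:

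1. Make the primary analysis event-driven, at the 96th PFS event assessed by the blinded committee. Give a projected date, about month 40–49 under the assumptions above, and describe three years as a projection.
2. Keep the three-year close, and restate the expected number of events (about 79–90) and the power (about 73–78%).

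The first option costs longer follow-up of patients already enrolled. The second costs a slightly lower stated power. Neither needs extra patients, and both are changes of wording.

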### Trial design

2.1

This is a prospective, open‐label, and randomized controlled trial. Patients who have been diagnosed with liver metastatic NETs (G1, G2) will be enrolled. Participants are randomly assigned in a 1:1 ratio to either the experimental group or the control group. Patients will be treated with surufatinib plus TAE in the experimental group, while patients in the control group will receive surufatinib monotherapy. This study will prospectively collect progression‐free survival (PFS), liver‐specific objective response rate (ORR), objective response rate (ORR), disease control rate (DCR), overall survival (OS), incidence of adverse reactions, and quality of life (QOL). Unless the patients experience PD or intolerable toxicity, each case should be treated for at least 8 weeks before efficacy evaluation.

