### Experimental group

3.1

Patients will receive 300 mg of surufatinib orally once a day, combined with TAE. The first TAE treatment should be performed within 14 days after starting surufatinib. During TAE, there is no need to stop surufatinib, and the frequency and interval of TAE should be determined by the interventional physician or multidisciplinary treatment. In the experimental group, patients should receive TAE at least once; for patients with a liver tumor burden exceeding 50%, it is recommended to perform TAE in stages to reduce complications. Each subject will receive treatment until disease progression, intolerable toxicity, or informed consent withdrawal (Figure 2).

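### PFS and OS are timed from the start of treatment rather than from randomisation, so the comparison risks not being of the groups as randomised

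*Protocol article*

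**What the plan says.** Under Trial design (2.1) the article describes the study so: "This is a prospective, open‐label, and randomized controlled trial". It adds: "Participants are randomly assigned in a 1:1 ratio to either the experimental group or the control group". The primary endpoint (4.1) is PFS as assessed by a blinded independent image review committee.

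The time origin is given only under Sample size and statistical analyses (5.5). There, "PFS is defined as the time from the beginning of treatment", and for survival, "OS will be evaluated from the start of treatment to the death of patients". No section starts either endpoint at randomisation, and none names an analysis population.

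Both arms take surufatinib (3.1 and 3.2). For the experimental arm, 3.1 adds: "The first TAE treatment should be performed within 14 days after starting surufatinib", and "In the experimental group, patients should receive TAE at least once". The article does not say whether treatment in that arm begins with the first surufatinib dose or with the first TAE.

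**The concern.** Randomisation makes the arms comparable at the moment of allocation. A clock that starts later, at an event that depends on what patient and physician do once the arm is known, no longer guarantees that comparability. Two consequences follow from the definition as printed:

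- A patient who never starts surufatinib has no time zero and so no PFS or OS time to enter into the Kaplan–Meier estimate or the log-rank test.
- Progression or death between randomisation and first dose precedes the clock and is not counted.

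The trial is open-label and only one arm involves an invasive procedure, so willingness to start could differ by arm. If those who do not start also differ in prognosis, the primary comparison is biased, in a direction that depends on which arm loses them.

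The undefined start of treatment adds an ambiguity. If it is the first surufatinib dose, the origin is the same event in both arms. If it were read as the first TAE, the clock would start later in the experimental arm only.

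**Working it through.** **1. The plan's own event count.** Inputs from 5.5: HR 0.6, power 80%, two-sided α 10%, 1:1 allocation. By Schoenfeld's formula,

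D = 4 (z₀.₉₅ + z₀.₈₀)² / (ln 0.6)² = 4 (1.645 + 0.842)² / 0.2609 ≈ 95,

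against a stated 96. The figure reproduces. The formula does not contain the time origin, so moving the origin to randomisation leaves the requirement where it is.

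**2. Loss of information.** The article gives no rate of randomised but untreated patients, so a loss of 0 to 10% of events is assumed. Power = Φ(√D × |ln 0.6| / 2 − 1.645), with |ln 0.6| = 0.511.

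| Events lost (assumed) | D | Power |
|---|---|---|
| 0% | 96.0 | 80.4% |
| 2% | 94.1 | 79.7% |
| 5% | 91.2 | 78.7% |
| 10% | 86.4 | 76.7% |

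**3. Selection.** This was simulated under no true treatment effect. From 5.5: 62 and 61 patients, 2 years of accrual, 3 years in total. Assumed: uniform accrual, exponential PFS, and a median of 10 months (between the 9.2 and 10.9 months that the Background cites for surufatinib). In each run a given share of patients are potential never-starters; they are removed from the experimental arm and kept in the control arm. The test is the log-rank test at two-sided 10%, so the nominal chance of falsely favouring the combination is 5%. There were 4,000 runs per setting.

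| Removed from experimental arm (assumed) | Hazard of never-starters ×1 | ×2 | ×3 |
|---|---|---|---|
| 5% | 5.5% | 6.6% | 7.9% |
| 10% | 5.0% | 8.9% | 10.5% |

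With nobody removed, the same simulation gave 5.2 to 5.6%. The simulation error near 5% is √(0.05 × 0.95 / 4000) ≈ 0.3 percentage points, so the two entries at hazard ×1 show no clear inflation. The error rate rises only when the loss is both one-sided and related to prognosis. Loss from the control arm only was not simulated; by the same reasoning it would push the other way.

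**4. The two readings of the start of treatment.**

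- First surufatinib dose: same event in both arms. A patient who starts surufatinib and later declines TAE already has a time zero and is kept.
- First TAE in the experimental arm: up to 14 further days are lost from the clock in that arm only, and a patient who never has TAE has no origin.

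**The case against.** The best defence is that the first surufatinib dose is the natural reading. It is the same event in both arms, the gap from randomisation is probably short, and few events should fall in it: 5.3 schedules imaging every 12 weeks with no scan between randomisation and first dose, and 5.1 requires a life expectancy above 3 months. The bias may then be small. A journal article may also leave analysis populations to a full protocol or SAP that is not shown. All of this stands and limits the size of the point. It does not remove it: the time origin is stated, not omitted, and an all-randomised population would sit badly with an endpoint that untreated patients do not have.

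Four stronger readings are tempting, but the document does not support them:

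- *Patients who decline TAE vanish from the primary analysis.* Section 3.1 places TAE after surufatinib has started, so on the natural reading they have a time zero. Whether they are analysed as assigned is a separate question about the analysis population.
- *The 5% dropout in 5.5 means about 3 patients per arm are lost* (0.05 × 62 = 3.1; 0.05 × 61 = 3.05). That figure is an allowance in the sample size and is not described as a rate of never starting.
- *The article excludes untreated patients.* It never says so; exclusion is a risk implied by the definition.
- *The experimental arm starts surufatinib later.* Section 3.1 times TAE relative to surufatinib, not the reverse, and no start delay specific to either arm is given.

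**Conclusion.** The point holds: the primary endpoint and OS are timed from an event after randomisation, in an open-label randomised trial, and that event is not defined for the two-component arm. The wording is certain; its consequence is not. On the assumed ranges, the cost is between nothing and about 4 percentage points of power (80.4% to 76.7%). The one-direction error lies between its nominal 5% and about 10.5%, and the upper figure needs 10% never-starters, all lost from one arm and with three times the hazard of the rest. The document gives no evidence of one-sided or prognostic loss. This is a should-fix correction to the endpoint definition, not a demonstrated bias in the result.

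**What to change.** In 5.5, define PFS and OS from the date of randomisation, in all randomised patients, analysed in the arm assigned whether or not surufatinib or TAE was given. Keep the start-of-treatment version, in treated patients, as a sensitivity analysis, and state there which event counts as the start in each arm. Make the change before outcomes are compared by arm, because a time origin chosen afterwards would itself be open to challenge.

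The cost is wording in the protocol and any SAP. The analysis needs each patient's randomisation date; the article does not mention this, but a randomised trial would be expected to hold it. The event target stays as it is. The one consequence to accept is that any gap between randomisation and treatment is then counted, in both arms.

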### The primary endpoint

4.1

The PFS was assessed by a blinded independent image review committee (BIIRC).

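### The PFS definition counts only cancer-related deaths, so any excess of deaths from TAE or from the combination would be left out of the primary comparison and could favour the TAE arm

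*Protocol article*

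**What the plan says.** Section 5.5 of the protocol article gives the only definition of PFS: time from the start of treatment "until the first observed disease progression or cancer‐related death". The abstract, section 4.1 and section 4.2 name the endpoint and who assesses it (a blinded independent image review committee for the primary analysis, the investigator for the secondary one). They do not define the event differently.

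Section 5.5 treats overall survival otherwise: "OS will be evaluated from the start of treatment to the death of patients", with no limit on cause. The restriction to cancer-related death therefore applies to PFS alone.

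On analysis, section 5.5 says: "The Kaplan–Meier method and a two‐tailed log rank test are used to evaluate PFS and OS". On treatment, section 3.1 says: "In the experimental group, patients should receive TAE at least once". The control group (section 3.2) takes surufatinib alone at the same starting dose. On blinding, section 2.1 says: "This is a prospective, open‐label, and randomized controlled trial".

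**The concern.** PFS is normally read as time alive and free of progression. Under the written rule, a patient who dies before progression from a cause not classed as cancer has not failed. That death is a competing event which the primary endpoint leaves out.

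This matters here because the arms differ by an invasive hepatic procedure. If TAE, or TAE given alongside surufatinib, causes deaths that surufatinib alone does not, they fall in one arm and are not counted against it. The background section itself says that no prospective trial has yet confirmed the feasibility of the combination, so an excess cannot be ruled out in advance.

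There is a second effect. Progression is read from images by blinded reviewers, but whether a death was cancer-related cannot be read from an image. In a patient with liver metastases, liver failure or bleeding after embolization could be assigned to tumour or to procedure. The restriction makes the primary endpoint depend on that judgement while treatment is known to those caring for the patient.

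**Working it through.** **1. The plan's own event target.** Inputs from section 5.5: "the hazard ratio (HR) was set as 0.6 with a β error of 0.2 and a two‐sided α level of 10" per cent, 1:1 allocation. Schoenfeld's formula gives

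events = 4 × (1.645 + 0.842)² / (ln 0.6)² = 4 × 6.183 / 0.2609 ≈ 94.8, so 95.

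The plan states 96, so the figure is reproduced. Power at 96 events = Φ(√96/2 × 0.511 − 1.645) = 0.804. The target depends on the HR, alpha and power, not on which deaths count, so widening the event definition leaves it unchanged.

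**2. Assumptions needed for the size.** The document gives neither a non-cancer death rate nor the control median used in the calculation. I assume a control median of 10 months, exponential times, a progression (or cancer-death) HR of 0.60, and follow-up of 12 to 36 months (2 years of enrolment within a 3-year study, section 5.5). The monthly event rates are ln 2/10 = 0.0693 in control and 0.6 × 0.0693 = 0.0416 in the TAE arm.

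**3. Early deaths in the TAE arm only.** A given percentage of experimental patients would die of a non-cancer cause in the first 3 months, independently of progression. Results are by simulation, as ratios of events per month of follow-up:

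| Non-cancer deaths, TAE arm | Of 62 | Of 61, control | HR as written | HR, any death |
|---|---|---|---|---|
| 2% | about 1 | 0 | 0.60 | 0.62 |
| 5% | about 3 | 0 | 0.60 | 0.65 |
| 8% | about 5 | 0 | 0.60 | 0.68 |

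The Cox HRs agree within 0.01.

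**4. Equal early deaths in both arms.** At 2% in each arm the all-death HR is 0.61. At 5% in each it is 0.61 by event rates and 0.62 by Cox. The gap from 0.60 is about 0.01, or 0.02 at most, so nearly all of the shift in step 3 comes from the assumed imbalance.

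**5. Deaths spread over follow-up, some in control.** With constant hazards, all-death HR = (0.0416 + h₁)/(0.0693 + h₀), where h is the monthly non-cancer death rate that makes the stated share of patients have such a death as first event. For 1% in control, h₀ = 0.00089.

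- 1% in the TAE arm: h₁ = 0.00068, HR = 0.602, power at 96 events 0.80.
- 3% (about 2 of 62): h₁ = 0.00207, HR = 0.0437/0.0702 = 0.622, power 0.75.
- 5% (about 3 of 62): h₁ = 0.00350, HR = 0.0451/0.0702 = 0.642, power 0.70.

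**6. Scale.** The standard error of log HR at 96 events is 2/√96 = 0.204. A move from 0.60 to 0.65 is ln(0.65/0.60) = 0.080, about 0.4 standard errors. The largest observed HR that is significant at two-sided 10% is exp(−1.645 × 0.204) = 0.715. A shift of this size would matter chiefly for a result close to that limit: with a progression HR of 0.70, step 3 gives all-death HRs of 0.72, 0.75 and 0.78.

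**The case against.** The strongest reply is that a reader might conclude that the comparison is biased towards TAE, and the document does not establish this. Four parts of the reply stand.

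- **No excess is documented.** The article gives no mortality figure for TAE, surufatinib or the combination. Section 3.1 says of high tumour burden that "it is recommended to perform TAE in stages to reduce complications"; that acknowledges complications, not deaths. If non-cancer deaths are rare or balanced, the effect is close to nil (working, step 4).
- **Drug toxicity is shared.** Both arms take surufatinib under the same dose-adjustment table. Only TAE or its interaction with the drug can produce an imbalance.
- **Censoring and attribution are inferred.** No censoring rule is given, and nobody is named to decide cause of death. Censoring is the natural consequence of Kaplan-Meier and log rank, and open-label attribution is plausible, but neither is stated. A death from liver failure or bleeding might be classed as cancer-related and so counted, which would shrink the effect.
- **The calculation does not show informative censoring.** The simulated deaths are independent of progression, so 0.60 is the correct cause-specific HR. What it shows is that the endpoint omits a competing harm.

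It can also be said that fatal harm would still appear in overall survival and adverse events. That is true, but it does not repair the primary endpoint. Nor can the point be left to an analysis plan: the event is defined in the article, and a plan that followed it would carry the same gap.

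**Conclusion.** The point holds in conditional form. The primary endpoint as written omits deaths not classed as cancer-related, and it rests on an attribution that image review does not protect. The omission could favour the TAE arm if procedure- or combination-related deaths occur in excess there; the document does not show that they will.

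The size is unknown. Under the stated assumptions, the all-cause HR would be about 0.62 to 0.68 against 0.60 as written for 2% to 8% early deaths in the TAE arm and none in control. It would be 0.60 to 0.64 for 1% to 5% against 1% in control with deaths spread over follow-up, and about 0.61 with equal early rates. Confidence is high on what the text says and on the possible direction, and low on the size.

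**What to change.** Reword the PFS definition in section 5.5, and in the full protocol and analysis plan to match: time to first RECIST 1.1 progression or death from any cause, whichever comes first. Progression is assessed by the blinded committee for the primary endpoint and by the investigator for the secondary one, with the same death rule in both. The version limited to cancer-related death may be kept as a sensitivity analysis.

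The cost is one sentence. Survival status is already recorded every 4 weeks (section 5.3), so no new data are needed, and the 96-event target stands. The downside is that the estimate may be slightly less favourable. If there is an excess of deaths in the TAE arm, power at 96 events falls below 80%, because the all-cause effect is then smaller.
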